### Participants and recruitment

Participants are being recruited from antenatal clinics across three large metropolitan hospitals in Greater Western Sydney, Australia. Information about the study is provided to all pregnant women attending their first antenatal visit (booking visit). At all Australian antenatal clinics the first booking visit is attended by midwives. While waiting to see the midwife, pregnant women are invited to participate by an independent recruiter (dental assistant). Women are eligible for recruitment (inclusion criteria): if they are more than 18 years of age; do not have cardiac disease that would warrant the need of antibiotics for dental treatment; have not received dental treatment in the current pregnancy; have a single pregnancy of more than 12 and less than 20 weeks of gestational age; do not have any known foetal anomalies or other risk factors (including history of preterm birth) that would place the pregnancy at risk of complications; and are able to attend regularly for dental treatment if required. Informed written consent is obtained by the dental assistant from pregnant women who meet the study inclusion criteria.

A self-administered pre-questionnaire is then provided to obtain baseline demographic data, dental/medical aspects of the women’s health (such as uptake of dental services, quality of oral health) and pre-test oral health knowledge. In addition, the Oral Health Impact Profile-14 (OHIP-14) questionnaire will also be administered. The OHIP-14 is a subjective measure of oral health that has been used extensively and found to be a precise, valid and reliable instrument (α=0.88) [27, 28]. It contains 14 questions assessed on a 5-point Likert scale and the total scores range from 0–56 with higher scores indicating poorer oral health. The OHIP-14 assists in validation and determining the sensitivity and specificity of the midwifery oral assessment tool by representing the ‘gold standard’ for identifying participants at risk of having oral health problems. Participants from non-English speaking backgrounds are provided, if required, interpreter services and translated oral health promotional materials.

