### Randomisation

Following consent and baseline data collection participants are allocated to the groups using block randomisation. This form of randomisation is recommended for large trials [29] and has been used in a number of recent trials in this research area [21]. A permuted block randomisation scheme with a random mixture of block sizes is used to set the allocation order, stratifying participants by hospital and presence of a dental problem. Block randomisation ensures that the number of participants in each arm of the trial will be evenly balanced [29]. Randomisation of participants is accomplished centrally using an independent computerised service which is accessed via the telephone at the time of recruitment.

Group allocation (IG1, IG2, CG) is represented by coloured stickers concealed in serially numbered opaque randomisation envelopes. After recruitment, baseline data collection and randomisation via telephone, the dental assistant hands over the randomisation envelope to the pregnant women, who then gives it to the midwife. All midwives at each of the hospitals are aware of which group each coloured sticker represents. To maintain allocation concealment and minimise selection bias the dental assistants are unaware of the colour codes and block sizes used for randomisation. In addition, the study investigators are blinded to group allocation. Due to the randomisation method, pregnant women attending on the same day receive different interventions.

To minimise any distress among pregnant women and maintain equipoise [30], oral health promotion material are provided via the dental assistant at recruitment to all trial participants. Women who refuse to participate are also provided with oral health promotional material. It is also possible that women attending the antenatal clinic on the same day might interact with each other which can lead to potential contamination (estimated at <5%) in the study. We are adjusting for this contamination during analysis [31] and have also included an item in the post questionaire asking if they have discussed their particpation in the study with other women attending the antenatal clinic at the same time. Analysis is being undertaken excluding such women.

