### Intervention groups

#### Intervention group 1 (IG1)

This group receives oral health promotional material at the time of recruitment. This group also receives a **midwifery intervention** (MIOH) which involves midwives providing the following at the 1^st^ antenatal visit:

*Oral health education*: Midwives re-emphasise the importance of maternal oral health.*Midwifery oral assessment:* As part of the antenatal check-up, midwives (trained in oral assessment) assess the oral health status of pregnant women using the following oral assessment tool. The tool consists of two questions and a visual inspection of the oral cavity (see Figure 1).

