##### Dental intervention

At the first appointment all the women undergo an initial dental oral assessment that includes medical history, followed by oral mucosal tissue examination, periodontal examination, dental caries examination and denture evaluation. A provisional diagnosis and treatment plan is made for those women having oral health problems. Once the consent for treatment is obtained, subsequent appointments are made in the second trimester to complete all the urgent treatment for women having dental problems. The second trimester (13–27 weeks) is considered a safe period to carry out necessary dental treatment^10^. The completion of treatment will take 1 to 3 additional visits depending on the treatment plan. Women having complex treatment needs such as root canal treatment are referred to the specialist for follow up care and are excluded from the study. After each examination participants are provided oral health education including oral hygiene instructions, brushing and flossing instructions and dietary counselling.

All women in the control group, intervention group 1 and group 2 (whether or not at risk of dental problems) undergo a final dental oral assessment by the study dentists at 28–38 week gestation period, the end point of this study. This examination is similar to the initial dental oral assessment and includes a detailed clinical examination. All women receive reminder cards from midwives followed up by telephone calls from the study administrative assistant to attend their final dental oral assessment. Pregnant women in the control group identified with a dental problem are referred to dental services after pregnancy. A post questionnaire having similar items to the pre questionnaire (demographic data, dental/medical aspects of the women’s health such as uptake of dental services, quality of oral health and post-test oral health knowledge), is administered to all women between 28–32 weeks. Contact details of private dentists who were consulted during pregnancy are also sought in the post questionnaire. The following methods are used to administer the post questionnaires: via the dental assistant/receptionist in the antenatal waiting room, via the midwife during the antenatal visit, over the phone when the final dental appointments are being made and via the study dentists at the final dental appointment.

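### The knowledge post-test, part of the primary hypothesis, may be collected by unblinded midwives or study dentists who delivered the intervention, and in a different mode from the pre-test

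*Protocol article*

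**What the plan says.** All references are to the Protocol article.

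- **Routes (Dental intervention).** The post questionnaire may be given "via the dental assistant/receptionist in the antenatal waiting room, via the midwife during the antenatal visit, over the phone" when the final dental appointment is being made, or "via the study dentists at the final dental appointment". The four routes are listed side by side; none is marked as preferred or as a fallback.
- **Content and timing (same section).** The form covers "uptake of dental services, quality of oral health and post-test oral health knowledge), is administered to all women between 28–32 weeks".
- **Who knows the group (Randomisation).** At recruitment, "the dental assistant hands over the randomisation envelope to the pregnant women, who then gives it to the midwife". The section adds: "All midwives at each of the hospitals are aware of which group each coloured sticker represents". By contrast, "the dental assistants are unaware of the colour codes and block sizes used for randomisation". The investigators are also blinded, and Data analysis says the same of the staff who run the analyses.
- **Who delivers the intervention.** In intervention group 1 (IG1), "Midwives re-emphasise the importance of maternal oral health", and midwives also assess and refer. The section on intervention group 2 (IG2) describes a similar midwifery component. The study dentists examine, treat and educate IG2 women.
- **Baseline mode (Participants and recruitment).** "A self-administered pre-questionnaire is then provided to obtain baseline demographic data", together with the knowledge pre-test.
- **Role of the outcome.** Primary hypothesis names knowledge as one of three outcomes. Outcome measures gives the pre- and post-test questionnaire as its only source.

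**The concern.** A knowledge test is open to influence from the person who gives it. A midwife who taught the material, or a dentist who gave the hygiene and diet advice, may clarify an item or repeat a message just before the woman answers. If that person also knows or recognises her group, the help can differ by arm. A woman rating her own oral health may likewise answer more favourably to someone who treated her.

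The intervention-control contrasts in knowledge are at stake, and with them one of the three claims in the primary hypothesis. No record outside the questionnaire could later correct the score. Blinded analysis does not help, because the influence would already be in the data. A larger sample does not help either: it makes a biased difference more precise.

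The second issue is mode. The pre-test is completed by the woman herself. At least one post-test route, the telephone, cannot be self-completion, and nothing in the article keeps the mix of routes equal across arms.

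**Working it through.** **1. The passages side by side**

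| Post-test route | Does this person know the group? | Did this person deliver the intervention? |
|---|---|---|
| Dental assistant or receptionist | Assistants do not know the colour code; receptionists are not described | No education described beyond the promotional material that all arms receive |
| Midwife at an antenatal visit | All midwives know the code, and a midwife receives each woman's envelope | Yes, in IG1 and IG2 |
| Telephone | Not stated | Not stated |
| Study dentist | Not stated, but they have seen those IG2 women who attended for their first assessment and treatment | Yes, in IG2 |

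So two of the four routes pass through staff who delivered the intervention. One of these groups holds the code; the other is likely to recognise its own patients. The IG2 section also lets women book through the dental assistant in the waiting room, so even an assistant without the code may learn that a woman is in IG2. That favours a form the woman completes and seals herself over reliance on the administrator's blinding.

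**2. The plan's own figures**

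Inputs from Sample size: uptake 30% against 50%, two-sided alpha 0.017, power 80%. With pooled variance and no continuity correction:

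n = [z₁₋α/₂ √(2p̄(1−p̄)) + z₁₋β √(p₁(1−p₁) + p₂(1−p₂))]² / (p₁−p₂)²

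= [2.387 × √0.48 + 0.842 × √0.46]² / 0.20² ≈ 123.7, rounded up to 124.

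Recruitment: 124 / (1 − 0.10 − 0.30) = 206.7, rounded up to 207; 3 × 207 = 621. The stated figures reproduce, and nothing in this point changes them.

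**3. What a differential shift would do (illustration on assumptions)**

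The article gives neither the share of women using each route nor any effect of the administrator. Let s be the share of an arm using an exposed route and d the shift in those women, in SD of the knowledge score. The net bias between an intervention arm (I) and control (C) is

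b = s_I d_I − s_C d_C.

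With no true effect and n = 124 per group, the chance of a significant pairwise result is

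Φ(b/√(2/n) − z₁₋α/₂) + Φ(−b/√(2/n) − z₁₋α/₂), where √(2/124) = 0.127 and z₁₋α/₂ = 2.387.

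| Assumed b (SD) | b / 0.127 | Chance of a significant result |
|---|---|---|
| 0 | 0 | 1.7% (nominal) |
| 0.1 | 0.79 | about 6% |
| 0.2 | 1.57 | about 21% |
| 0.3 | 2.36 | about 49% |

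These are arm averages. If half of an intervention arm used an exposed route and control women were unaffected, b = 0.2 would need a shift of 0.2 / 0.5 = 0.4 SD in the women exposed. If control women were shifted equally and used the route equally often, b would be 0.

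**The case against.** The strongest reply is that the text permits a harmless reading. Giving a form through the midwife may mean only handing it over, as the parallel dental assistant or receptionist route suggests. The pre-test was self-completed and the post questionnaire has similar items, and an article may leave completion instructions to the full protocol. This stands in part: if the form is self-completed out of the midwife's sight, most of the scope for prompting goes. But the article does not say that the post questionnaire is self-completed, and it places this route within the antenatal visit.

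Three stronger readings are tempting and are not supported:

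- **A reader might infer that each woman is tested by the midwife who taught her and still knows her group.** The article does not say that the same midwife sees her at 28–32 weeks, or that the sticker is still in view then. Knowing the code is not the same as knowing one woman's group months later. What stands is that nothing prevents either.
- **A reader might infer that the bias acts only in the intervention arms.** Control women also see midwives, hand over envelopes, receive material advising a dental visit, and may use every route. The likely direction favours the intervention, but neither sign nor size is fixed.
- **A reader might infer that the uptake contrast is inflated as well.** Uptake also draws on returned checklists, the study clinic database, follow-up of referrals, the final assessment and contact with private dentists (Referrals; Outcome measures). Control women have fewer of these sources before the endpoint, so self-report matters more for them, but that does not establish inflation.

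A practical objection also has some weight: several routes help to limit loss, and the plan already allows for 30% at the endpoint.

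**Conclusion.** The point holds as a stated but avoidable risk, not as a demonstrated bias. The article allows a primary-hypothesis outcome with a single source to be collected by midwives who hold the allocation code and teach in IG1 and IG2, or by dentists who treat and educate IG2 women. The mode may also differ from the pre-test. Knowledge is the main outcome affected and self-rated oral health, which Primary hypothesis does not name, the second; the concern is weaker for uptake.

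The size cannot be derived from the document. The rates of 6%, 21% and 49% rest entirely on assumed net shifts of 0.1, 0.2 and 0.3 SD. They show only that a modest differential shift would matter at this sample size. The routes are stated in the article, so this is not a detail left to an analysis plan, and no analysis plan could repair the collection.

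**What to change.** 1. In all three arms, have women complete the post questionnaire themselves in the waiting room, before they see the midwife or the study dentist, and return it in a sealed envelope to the dental assistant or receptionist.
2. Remove midwives and study dentists as administrators.
3. Keep one telephone call as the only fallback for women who have not returned a form, read from a fixed script by a caller unaware of group.
4. Record mode and administrator on every form, so that a sensitivity analysis by mode is possible. If forms have already come in through midwives or dentists, record this for them too where it can be established.

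The cost is a change of procedure wording, envelopes and a script. Reception and telephone contact are already in use, though the caller's unawareness of group would have to be arranged. The sample size is unchanged. The downside is some additional calls and possibly a few more missing forms, to be watched against the 30% endpoint loss already allowed for. A telephone fallback still differs in mode from the pre-test, and women know what care they received, so the change reduces the risk without removing it.

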##### Education for midwives and dentists

Prior to the commencement of the trial all midwives from participating hospitals undertake the specific oral health education program endorsed by the Australian College of Midwives [18]. Midwives have to complete the program and competency assessment to ensure that they have adequate knowledge of oral health and are competent to undertake an oral visual inspection. Prior to the trial the two study dentists employed for the study participate in a two hour education workshop where they are trained by an experienced dental clinician to follow a standardised dental protocol during pregnancy. Training is also provided on the use of the oral health status measures. Inter-rater reliability testing of the dentists’ oral health assessments will be examined using 10 mock oral assessments.

##### Control group (CG)

This group receive oral health promotional material at recruitment. This material focuses on the importance of oral health, good oral health practices (dietary counselling, fluoride use, quitting smoking) and advice on seeing a dentist during pregnancy. They do not receive any intervention until the completion of the trial. At the point of completion, these women are referred to dental services, if required. Figure 2 outlines the design of the MIOH-DS trial which follows the principle of equipoise.

**Figure 2 Fig2:**
[figure not shown]
**Detailed design of MIOH-DS trial.**

### Outcome measures

The following outcome measures—estimates of uptake of dental services, oral health knowledge, quality of oral health, oral health status and birth outcomes are proposed for this trial:

*An estimate of the uptake of dental services* will be obtained from the following sources: the returned checklist; the database of the study dental clinics; data from the post questionnaire, following up all referrals by midwives and at the final dental oral assessment period; contacting private/health fund dentists used by the women (contact details obtained from the post questionnaire and returned checklist).*Oral Health Knowledge* will be assessed using a pre-test and post-test questionnaire (tested in the pilot study) [19] and administered to pregnant women at the recruitment and final dental oral assessment period respectively.*Quality of oral health* will be assessed using the following validated item [37] to be included in the pre and post questionnaire: ‘On a scale of 1–5 where 1= poor and 5=excellent, How would you describe the health of your teeth and mouth?*Oral health status* will be assessed using several measures—gingival inflammation and bleeding, clinical attachment loss, level of plaque and dental caries*.* These measures are to be used at both the dental oral assessments: –Gingival inflammation and bleeding is assessed using The Sulcus Bleeding Index [38] and is used to measure the degree of inflammation and bleeding in the gums;–Clinical Attachment Loss (CAL), measures the degree of CAL (periodontal pocket depth, gingival recession and calculus) and is assessed using a calibrated periodontal probe [39];–Level of plaque is measured using The Approximal Plaque Index [38].–Dental caries will be determined by the Decayed, Missing, Filled Teeth (DMFT) Index [40]. The DMFT index is used to monitor the changes in the various components. If the intervention is successful decayed teeth will have been filled or removed.

*Birth outcomes*: Gestational age at birth and birth weight is obtained from the ObstetriX data system (ODS) [41] which is a reliable data source (Kappa =0.75) using data items/definitions from the NSW Perinatal Data Collection (population based surveillance system covering all births in NSW public/private hospitals). Data from ODS is accessed using the women’s medical record numbers and date of birth (collected at recruitment) through local data custodians.*Specificity and sensitivity of midwifery assessment:* To further confirm the practicality of this tool, the midwifery oral assessment tool (2 items) will be compared with two gold standard measures- the OHIP-14 questionnaire (completed at the time of recruitment: pre-questionnaire) in IG1 and IG2 and the initial dental oral assessment conducted by the two study dentists in IG2. This will allow for women with and without oral health problems (the proportion of true and false positives and the proportion of true and positive negatives) to be identified. The OHIP-14 questionnaire has been used as the gold standard in previous studies to validate oral assessment tools [36, 42]. The two study dentists are trained to follow a standardised dental protocol during pregnancy. Adherence to the protocol is being evaluated by assessing the returned checklist.

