## Methods/Design

### Overall study design

The MIOH-DS study is being assessed using a three arm multicentre randomised controlled trial across three recruitment sites. Participants are randomly assigned to the intervention (two groups) or control groups with a goal of n=124 in each group at the time of post intervention follow up. There are two assessment periods: baseline (12–20 weeks gestation) and post assessment (28–42 weeks gestation). The study has been funded by the National Health and Medical Research Council of Australia for three years.

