#### Referrals

In this group, all pregnant women assessed to be at risk of poor oral health are referred to current dental services (either private, public or health fund) for treatment. The referral letter provided to pregnant women includes a covering letter and a survey/checklist—date of first visit, total number of visits required, treatment completed (item numbers), and dentists contact details—to be completed by the dentists and returned to the study investigators via fax. Information on the survey/checklist is also sought from private dentists whose contact details are provided by pregnant women in the post questionnaire. The checklist helps to assess the uptake of dental services, the common treatment requirements and associated dental costs, all of which are vital information to inform future economic evaluations and subsequent state and national policy in this area.

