##### Intervention group 2 (IG2)

This group receives oral health promotional material at the time of recruitment. This group also receives a **midwifery and dental intervention** (MIOH-DS). The **midwifery intervention** will be similar to Intervention group 1. However, in this group all pregnant women, regardless of whether they are assessed to be at risk of having dental problems or not by the midwife, are referred (referral letter with checklist) to the dentists employed for this study for an initial dental oral assessment (part of the dental intervention). This allows for further testing of the midwifery oral assessment tool and to gather baseline oral health data. Pregnant women who consent are provided vouchers that entitle them to priority access to free oral assessment and treatment by the study dentists at dental clinics in the recruitment hospitals. This service is an extra service created specifically for this study and is co-ordinated by the study team. The voucher is valid for 4 weeks from booking visit date to encourage pregnant women to see the dentist promptly. Pregnant women can make the dental appointment by calling the telephone number provided with the referral letter or contacting the dental assistant in the antenatal waiting room.

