### Sample size

Sample size estimation is calculated on the outcome measure uptake of dental services using the assumption that 30% of pregnant women in the control group will access dental services during pregnancy (based on our survey [23] and existing Australian studies [10, 43, 44]. We expect the MIOH (IG1) and MIOH-DS service (IG2) will improve the uptake of dental services. The MIOH intervention is considered successful if at least 50% of the pregnant women in IG1 and IG2 will access dental services during pregnancy, a difference of 20% between the groups. To detect a difference of at least 20% between the groups with a two-sided test of proportions, alpha of 0.017 (three comparisons 0.05/3), and 80% power we determine using a statistical software that we require at least 124 patients in each group. Taking into account 10% attrition (refusal after randomisation-based on the results of our pilot survey) and 30 % loss at the endpoint (based on trials in this area - range 2-30%) [21] we will need to recruit 207 participants in each group.

Sample size was also calculated on the outcome measure oral health status using the assumption that 50% of pregnant women in the control group will have gingival bleeding (based on trials in this area) [21]. A 30% improvement in oral health status is expected in IG1 and IG2 (30% reduction in gingival bleeding). To detect a difference of at least 30% between the groups with a two-sided test of proportions, alpha of 0.017, and 80% power we determine using statistical software [45] that we require at least 52 patients in each group. Taking into account 10% attrition and 30 % loss at the endpoint we will need to recruit 87 participants in each group. Based on these estimations we will require a total of 621 participants for the trial (207 in each group). Interim analyses will be used to re-check the sample size after the first 100 women are recruited.

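### Uptake of dental services, the outcome that sizes the trial, is ascertained from sources that differ by arm, and study-scheduled dental visits are not excluded from it

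*Protocol article*

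**What the plan says.** **Sources.** The Outcome measures section lists "the returned checklist; the database of the study dental clinics; data from the post questionnaire, following up all referrals by midwives". The same sentence goes on to the final assessment period and to contact with private or health fund dentists, traced through the questionnaire and the checklist.

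**Who generates which record.** In IG1, "all pregnant women assessed to be at risk of poor oral health are referred to current dental services", and the checklist is enclosed with that referral (Referrals). In IG2 every woman, at risk or not, is referred with a checklist to the study dentists for an initial assessment. The stated reason is: "This allows for further testing of the midwifery oral assessment tool and to gather baseline oral health data". The same section describes that assessment as belonging to the dental intervention and the clinic as an additional service set up by the trial (Intervention group 2). Control women are referred only once the trial is complete (Control group).

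**What all arms share.** The post questionnaire, which asks about uptake, "is administered to all women between 28–32 weeks". All three arms also attend a final assessment by the study dentists at 28–38 weeks (Dental intervention). The Overall study design section gives a third window: "post assessment (28–42 weeks gestation".

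**Role of the outcome.** The Sample size section assumes "30% of pregnant women in the control group will access dental services during pregnancy" and defines success as "at least 50% of the pregnant women in IG1 and IG2 will access dental services during pregnancy", with "alpha of 0.017 (three comparisons 0.05/3), and 80% power".

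**The concern.** Two features of the definition bear on the contrast that decides success.

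1. **Unequal ascertainment.** Some listed sources cannot record a control woman's visit during the trial. Those that can all depend on her still being in contact late in pregnancy. A woman in IG1 or IG2 who drops out after seeing a dentist can still be counted from a checklist or a clinic record. A control woman in the same position cannot. Where these records add women, they mainly add attenders, and only in the referred arms.

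2. **Study-scheduled visits.** Nothing in the definition sets aside the final assessment, which is a dental visit in every arm. Nor does it say whether IG2's initial assessment counts, although the study clinic database is a listed source. The IG2 contrasts therefore mix the effect of offering free, prompt care with attendance at an examination that the trial scheduled partly for its own data.

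The article also gives no single gestational limit up to which a visit counts. The three windows apply to every arm, so this is not in itself a bias between arms, but a common definition needs one limit.

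**Working it through.** **The plan's own figure.** For 30% against 50%, two-sided alpha 0.017 and 80% power, with pooled variance under the null and no continuity correction:

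n = [2.387 × √(2 × 0.40 × 0.60) + 0.842 × √(0.30 × 0.70 + 0.50 × 0.50)]² / 0.20² = 123.7, so 124 per group.

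Recruitment: 124 / (1 − 0.40) = 206.7, so 207. Both stated figures reproduce.

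**Ascertainment by arm**

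| Source | Control | IG1 | IG2 |
|---|---|---|---|
| Post questionnaire and dentists named in it | yes | yes | yes |
| Final assessment period | yes | yes | yes |
| Returned checklist | no | at-risk women | all women |
| Follow-up of midwife referrals | no | at-risk women | all women |
| Study clinic record before the final assessment | no | no | all women referred |

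**Illustration of part 1.** From the documents: p = 0.30 (control uptake), 30% endpoint loss, 207 per arm, alpha 0.017. Assumed, because the documents give no figure: true uptake is 30% in both arms, the 30% loss is read as non-return of the questionnaire, and a fraction c of attenders who did not return it is captured by arm-specific records.

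- Control: 0.7 × 207 = 144.9 women with data, observed uptake 30%.
- Referred arm: observed uptake = (0.7p + 0.3pc) / (0.7 + 0.3pc), in 207 × (0.7 + 0.3pc) women.
- Rejection probability: two-sided pooled z test on these two proportions and sample sizes.

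| c | Observed uptake, referred arm | Type I error |
|---|---|---|
| 0 (equal capture) | 0.210/0.700 = 30.0% | 1.7% |
| 10% | 0.219/0.709 = 30.9% | 1.9% |
| 25% | 0.2325/0.7225 = 32.2% | 2.6% |
| 50% | 0.255/0.745 = 34.2% | 5.5% |
| 100% | 0.300/0.790 = 38.0% | 17.9% |

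The spurious difference is thus about 1 to 8 of the 20 points sought.

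**Illustration of part 2.** Let q be the share of IG2 women who would not otherwise see a dentist and who attend only the initial study assessment. Counted uptake is 0.30 + 0.70q.

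- q = 5%: 33.5%
- q = 10%: 37%
- q = 20%: 44%
- q = 0.20/0.70 = 28.6%: 50%, the success threshold

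q is an assumption. This shows how far the IG2 result depends on whether that visit counts. It does not measure bias.

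**The case against.** A reader might infer that IG1 and IG2 must beat control even with no true effect. The documents do not support that, for four reasons.

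- **Trial-run visits are not confined to the referred arms.** Control women also see the study dentists at the final assessment. If that visit were counted, control would rise too and the contrast would shrink. IG1 has no trial-run visit of its own before then.
- **Control is not without sources.** The questionnaire has four routes of administration, and women in every arm receive reminder cards and calls for the final assessment. Private dentists are contacted from details given in any arm. The IG1 bias is zero if capture is equal. It is small if capture is low, and low capture is plausible: only at-risk IG1 women carry a checklist, and outside dentists must choose to fax it back. Referral follow-up may also record non-attendance, which the illustration ignores.
- **The IG2 initial visit is part of what is randomised.** Attendance is voluntary, and women who go because a free visit is offered are responding to the intervention. Higher uptake from a broader offer is partly a real effect.
- **The windows overlap, cover different items and apply to all arms.**

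The article also does not say how the sources are to be combined.

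All of this stands and limits the point. It does not remove it. The listed sources still differ by arm, every control source still requires retention, substantial loss is expected, and no scheduled visit is set aside.

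**Conclusion.** The point holds in limited form. Uptake is ascertained unequally by arm, in a direction that can favour IG1 and IG2. The size cannot be derived from the documents. With true uptake of 30% in both arms and 70% questionnaire return, capture of 10%–100% of the remaining attenders gives about 31%–38% observed against 30%, and a type I error of about 2%–18% instead of 1.7%. The upper end needs nearly complete capture of lost attenders, which is more plausible in IG2 than in IG1.

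Separately, the definition leaves open whether study-scheduled visits count, so the IG2 contrasts mix the effect of the offer with a scheduled examination. It would be wrong to treat IG2's initial visit as pure artefact. The sample size arithmetic is correct.

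**What to change.** Define primary uptake in the same words for all arms:

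- Any dental visit other than the final study assessment, up to one stated gestational cut-off that the questionnaire covers in every woman. The three post-assessment windows should be reconciled at the same time.
- Numerator and denominator from the post questionnaire, the source every arm has.
- Checklists, clinic database and referral follow-up used only to confirm answers in women who returned it, not to add women.
- All-sources uptake reported as a sensitivity analysis.

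Keep IG2's initial assessment in the primary definition, as part of the randomised offer. Add a sensitivity analysis under one rule applied to every arm, for example counting uptake only when treatment was given.

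Do not discard IG2 visits on the basis of the midwife tool score. Controls have no score, and the same check-up would still count in the other arms. For example, assume 60% of women at risk, 60% attendance when referred and 30% otherwise. IG1 is then 0.6 × 0.6 + 0.4 × 0.3 = 48%. IG2 is 60%, but would fall to 0.6 × 0.6 = 36% if no visit by a score-0 woman were counted. That is a bias against IG2.

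**Cost.** This is a change of wording, and the data are already collected. The primary figure relies more on self-report, recorded attendance in non-responders is lost to it, and uptake in IG1 and IG2 may look less favourable. If return of the questionnaire differs by arm, some selection remains, which the all-sources analysis helps to show. The 124/207 per group is unchanged while 30% against 50% is kept. The documents do not say whether the 50% was meant to include IG2's study-clinic visits, and this should be stated.
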